### Sample size calculation

#### Observational and interventional studies

The calculation of the number of caregivers required was based on both the design and the primary objectives of the intervention study, with noncompetitive recruitment according to each group of diseases (randomization performed 1:1 per group). We aim to demonstrate the efficiency of the intervention in each of the five groups of diseases. The hypothesis is that the intervention proposed will improve the HRQoL of caregivers on at least one of the two summary scores of the MOS SF-36 (i.e., physical health and/or mental health).

The minimal clinically important difference (MCID), which is the smallest change in an outcome that a patient would identify as important, was fixed at 5 points [21].

The null hypothesis (H0) is that there will not be a difference of at least 5 points between the two arms in at least one HRQoL summary score at 1 year; while the alternative hypothesis (H1) is that there will be a difference of at least 5 points between the two arms in at least one HRQoL summary score at 1 year.

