With a bilateral alpha risk of 5 % and a statistical power of 90 % to detect a difference of at least 5 points (standard deviation (SD) = 25), and adjusted to take account of the number of statistical tests and maintain an overall alpha type one error rate of 5 % (Bonferroni adjustment):With two dimensions of HRQoL, α’ = α/2 = 0.05/2 = 0.025With five groups of diseases, α” = α’/5 = 0.025/5 = 0.005 (cancer (breast, prostate, colorectal); neurodegenerative disease (Alzheimer’s disease and similar diseases); AMD; neurovascular (stroke); cardiac (heart failure))At least 1684 caregivers should be randomized in each disease group. However, we anticipate lower recruitment in the heart failure group. Accordingly, only 488 caregivers will be randomized (bilateral α type I error of 0.005 and statistical power of 80 %) to demonstrate a difference of at least 5 points (SD = 15). Thus, it will be necessary to include and to randomize 4 × 1684 = 6736 caregivers, plus 488 in the heart failure group, representing a total of 7224 caregivers. An interim analysis will be planned to reject either H0 or H1 (Alpha Spending Function and O’Brien-Fleming Boundaries) when half the caregivers have been included with 1 year of follow-up in each of the subgroups. To allow for 5 % of loss to follow-up, it will be necessary to include and randomize an additional 380 caregivers, resulting in an overall total of 7604 caregivers (1750 caregivers for each of the four large groups of diseases and 604 for the heart failure group)

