#### Analysis

Analyses will be performed using SAS (version 9.4) (SAS Institute Inc., Cary, NC, USA), R (version 3.2.2) [49] and Stata (v13) (StataCorp LP, TX, USA) software. The statistical analysis plan for the primary and secondary objectives will be written before the database is locked.

All analyses will be on a modified intention-to-treat principle, i.e., including all randomized informal carers regardless of the eligibility criteria and intervention received, with MOS SF-36 scores available at baseline and 1 year. Analyses for the interventional study will be done on an intention-to-treat basis. After Bonferroni adjustment, statistical significance will be fixed at the 0.005 level for primary analyses, and at the 0.05 level for the secondary objectives.

An interim analysis is planned when half of the patients will be included to reject or not H0 (efficacy) or H1 (futility); the Alpha Spending Function with O’Brien-Fleming Boundaries will be used to determine the alpha-level significance at the interim and at the final analysis using EAST® software (Cytel Software Corporation, Cambridge, MA, USA) [50]. The corresponding confidence interval will be computed (1 − alpha level).

Sociodemographic and clinical characteristics will be described at inclusion using frequency (percent) for qualitative variables and mean (SD), or median (min–max) for continuous variables. Data will be compared between randomization arms using the Student *t* test or the nonparametric Mann-Whitney test, or analysis of variance (ANOVA) or the Kruskal-Wallis test for continuous variables and the Chi-squared or Fisher’s exact tests for qualitative variables, as appropriate. Scores will be described at each follow-up time point using mean (SD) and median (min–max) in each arm.

After describing missing data and investigating the mechanism of missing data profiles, imputation will be performed using a multiple imputation method by sensitivity analysis after checking normality, and univariate and multivariate ANOVA adjusted for baseline score will be performed to compare the two summary scores of the SF-36 questionnaire at 1 and 2 years.

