Multivariate analyses will be performed including at least the stratification criteria for randomization, as well as variables associated with HRQoL at the 10 % level by univariate analysis. HRQoL data will also be longitudinally analyzed using a mixed model of analysis of variance for repeated measures (or pattern mixture models in case of a missing-not-at-random profile) in order to test an arm effect, time effect and an interaction between arm and time, as well as the effect of other relevant parameters (HADS, coping, clinical parameters, etc.). Some random effects on patients will also be introduced into the model in order to reflect individual trends. Burden, coping and HADS will also be modeled as time-dependent covariables in another model. Time to HRQoL score deterioration will be estimated using the definitions of both Bonnetain et al. [51] and Hamidou et al [52]. Item Response Theory, cluster analyses, structural equation modeling as well as classical factorial analyses will be conducted as complementary analyses to define and validate longitudinal profiles of caregivers. All these analyses will be repeated in each subgroup defined by stratification (including cancer localizations) for sensitivity analyses.

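### Two analyses are prescribed for the primary 1-year comparison with no lead model, and the adjusted one takes its covariates from a 10% screen on the outcome; separately, the secondary longitudinal arm effect may be attenuated

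*Protocol article*

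**What the plan says.** The Interventional study section makes the between-arm comparison of the SF-36 mental and physical summary scores at 1 year the main objective. The Analysis section states that "statistical significance will be fixed at the 0.005 level for primary analyses", following a Bonferroni split over two scores and five disease groups.

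For these scores, at 1 and 2 years, the Analysis section prescribes that "univariate and multivariate ANOVA adjusted for baseline score will be performed to compare the two summary scores". It ranks neither version above the other. It then describes the adjusted version: "Multivariate analyses will be performed including at least the stratification criteria for randomization, as well as variables associated with HRQoL", the last group being picked at the 10% level by univariate analysis. The stratification criteria are a minimum set, and the screened variables are not restricted to those measured at baseline.

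The same section adds a repeated-measures mixed model that tests arm, time and their interaction, along with other parameters, of which HADS and coping are named. It continues: "Burden, coping and HADS will also be modeled as time-dependent covariables in another model". The Interventional study section lists the longitudinal quality-of-life comparison as a secondary objective. It also lists coping, HADS and perceived burden as secondary outcomes to be compared between arms.

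**The concern.** There are two separate issues.

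1. **Primary comparison.** There are ten primary tests (two scores in each of five disease groups), and each has two candidate p-values. The adjusted one depends on a covariate set that is unknown until the outcome data are in and may differ from one test to the next. If the two p-values fall on opposite sides of 0.005, the protocol does not say which counts. The Bonferroni level is exact for one pre-specified test per hypothesis, not for the better of two.

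2. **Secondary longitudinal comparison.** The social worker's support is meant to ease distress and burden. If an arm coefficient is reported from a model that conditions on HADS, coping or burden measured after randomisation, whatever part of the effect runs through them is removed from that coefficient. The result is then no longer the effect of offering the intervention.

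**Working it through.** **Inputs from the protocol (Sample size calculation and Analysis).**
- Level: 0.05 / 2 / 5 = 0.005 per test, two-sided ("bilateral α type I error of 0.005").
- Four large groups: "to detect a difference of at least 5 points (standard deviation (SD) = 25"), 90% power, stated size 1684 per group.
- Heart failure: "to demonstrate a difference of at least 5 points (SD = 15"), 80% power, stated size 488.

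**Reproducing the plan's own figures.** For two means, n per arm = 2 × (SD/difference)² × (z for alpha + z for power)².
- Large groups: 2 × (25/5)² × (2.807 + 1.282)² = 836 per arm, 1672 in total, against 1684.
- Heart failure: 2 × (15/5)² × (2.807 + 0.842)² = 240 per arm, 480 in total, against 488.

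Both agree within 3%. The calculation is one unadjusted two-sample comparison per hypothesis, so choosing between two analyses is not part of the design.

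**Error if either analysis may be used.** Let R² be the share of residual variance, after baseline adjustment, that the extra covariates explain (an assumption; the protocol gives no figure). With covariates independent of arm, the two test statistics have correlation √(1 − R²) under the null. The error is P(|Z1| > 2.807 or |Z2| > 2.807).

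| Assumed R² | Correlation | Error per test | Ten tests (sum) |
|---|---|---|---|
| 0.1 | 0.949 | 0.0069 | 6.9% |
| 0.2 | 0.894 | 0.0077 | 7.7% |
| 0.4 | 0.775 | 0.0086 | 8.6% |

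The last column is a Bonferroni sum and so an upper bound, to be set against 10 × 0.005 = 5%. The interim look is ignored throughout.

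**Simulation of the 10% screen itself.** Assumptions: 488 caregivers, SD 15, no arm effect, baseline correlation 0.5, 15 candidate baseline covariates of which five are prognostic (jointly 5, 15 or 30% of total variance), 6000 runs.

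| Prognostic share | Baseline-only model | Screened model | Smaller of the two p-values |
|---|---|---|---|
| 0.05 | 0.0060 | 0.0060 | 0.0075 |
| 0.15 | 0.0060 | 0.0060 | 0.0097 |
| 0.30 | 0.0043 | 0.0057 | 0.0087 |

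The simulation standard error at 0.005 is √(0.005 × 0.995 / 6000) ≈ 0.0009. Either model alone is therefore compatible with 0.005, and the excess appears only when the better one is taken.

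**Attenuation by a post-randomisation covariate.** Assumptions: total effect 5 points, SD 25, 1684 caregivers, one mediator, no confounding between mediator and outcome. The expected adjusted coefficient is 5 × (1 − share mediated).

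| Assumed share mediated | Expected | Simulated, mediator in model |
|---|---|---|
| 0 | 5.00 | 4.9 |
| 25% | 3.75 | 3.7 |
| 50% | 2.50 | 2.6 |
| 75% | 1.25 | 1.2 |

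Without the mediator in the model, the estimate stayed at 4.9 to 5.0 in every case. The shares are illustrative, as the protocol gives no basis for one.

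**The case against.** **The SAP may settle the order.** The protocol says the SAP will be written before database lock, and a condensed article need not list covariates or rank models. That stands as a reason not to fault the article for brevity. It does not remove the point, because the article itself states the outcome-driven rule and the two unranked analyses. A SAP that followed it faithfully would inherit both.

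**A simple analysis followed by an adjusted one is a common sequence.** True, and nowhere does the text say that significance may be claimed from either. The error figures are conditional on that freedom. Nor does the screen as such inflate the error: on baseline variables, the screened model alone held its level.

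**The screen need not use treatment codes.** Association with quality of life can be examined on pooled data. The protocol does not say that arm is known at that stage, so nothing here rests on unblinded screening.

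**The longitudinal models also serve the cohort.** The observational aim is to profile caregivers by quality of life, coping, mood and burden, and time-dependent covariates are legitimate for that. The time-dependent model is described as a separate one, and no arm effect is promised from it. In the mixed model that does test arm, HADS and coping might be baseline values. The text does not say.

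**A tempting stronger reading.** A reader might infer that mediators bias the primary result. The documents do not support this: HADS, coping and burden are not named in the 1-year baseline-adjusted ANOVA. They could reach it only if the screen admitted post-randomisation measures, which the wording permits but does not state. Nor should the attenuation be turned into a loss of power at 0.005. It concerns a secondary analysis, which the protocol tests at 0.05.

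**Conclusion.** The concern holds in this limited form. For the primary 1-year comparison, the protocol names two analyses and no lead, and fixes an outcome-driven covariate screen that is not confined to baseline variables. The consequence is an unfixed primary result, not a demonstrated bias in it. If either analysis could carry the claim, the error per test would rise from 0.005 to about 0.007 to 0.009, and the overall level from 5% to at most about 7 to 9%. This rests on the assumption that the extra covariates explain 10 to 40% of residual variance. The simulation of the screen gave a similar range, 0.0075 to 0.010 per test.

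The second part is weaker and confined to a secondary objective. The longitudinal arm effect would be attenuated if it were taken from a model with post-randomisation HADS, coping or burden. The size depends wholly on the share of the effect that they mediate, which is unknown. The point merits correction before the data are analysed; it does not call the design or sample size into question.

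**What to change.** - Name one primary model for each disease group and score at 1 year: ANCOVA with arm, baseline score and that group's minimisation factors, tested at the primary level. Designate every other version as a sensitivity analysis.
- Remove the 10% screen from all arm comparisons. If some form of it is kept, confine it to a pre-listed set of baseline variables in a sensitivity analysis. It can remain in the descriptive modelling of the cohort.
- In any model from which an arm effect is reported, allow only baseline values of HADS, coping and burden.
- Label the model with time-dependent HADS, coping and burden as explanatory, serving the cohort aim, with no claim about arm.

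The cost is protocol and SAP wording. The sample sizes and the 0.005 level do not change. The minimisation factors are already defined in the Randomization procedure section, and no new data are needed.

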#### Interventional study

A randomized interventional trial in a 1:1 ratio will be conducted within this cohort to evaluate the effect of a pragmatic supportive intervention on caregivers, provided by a social worker and an information booklet (intervention arm) versus the control arm, where caregivers will only receive the information booklet, without social worker support. The intervention will be conducted during the first 2 years of entrance into the caregiver’s role. The intervention proposed here mobilizes social workers of the Departmental Councils, of the General National Retirement Fund (CARSAT Burgundy-Franche-Comté) and of the Community Social Action Association (CCAS of Dijon). All institutions providing social workers are officially involved in the study and all social workers are trained in the management of older people, characteristics of caregiving relationships and in ICE cohort study procedures. The structure and purposes of the social worker’s intervention are described in Table 1. The main objective is to compare the mental and physical health summary scores on the MOS SF-36 at 1 year between the two groups. Secondary objectives are to compare the following parameters between groups: (1) the mental and physical health summary scores of the MOS SF-36 at 2 years, (2) all HRQoL dimensions of the MOS SF-36 at 1 year and at 2 years, (3) longitudinally: all HRQoL dimensions of the MOS SF-36 and the CarGOQoL questionnaire (only for caregivers of the cancer patient group), (4) coping strategies (as assessed by the coping scale developed by Borteyrou, Truchot and Rascle [35]), (5) anxiety-depression (as assessed by the HADS), (6) social support (as assessed by the SSQ6) and the perceived caregiver burden (as assessed by the Zarit Caregiver Burden Interview) and (7) to assess from a societal perspective the incremental cost-effectiveness ratio (ICER) of the intervention of a social worker for caregivers. The ICER will be expressed in terms of quality-adjusted life years (QALYs) gained based on a utility score that will be calculated based on the EuroQoL EQ-5D questionnaire, the SF-6D which is composed of 11 items of the SF-36 questionnaire and the Center for Epidemiologic Studies-Depression Scale (CES-D) questionnaires and economic survey.

**Table 1 Tab1:** Content and purposes of the pragmatic intervention by a social worker in the intervention group of the nested randomized trial for caregivers

Format of the intervention:

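### The longitudinal analysis switches to pattern mixture models only if data are found missing not at random, which observed data cannot show; an MNAR sensitivity analysis should be reported in every case

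*Protocol article*

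**What the plan says.** Protocol article, Analysis: the longitudinal scores are to be analysed with a repeated-measures mixed model, "or pattern mixture models in case of a missing-not-at-random profile", the purpose being "in order to test an arm effect, time effect and an interaction between arm and time". The bracket offers the pattern mixture model as an alternative to the mixed model, not as a companion to it.

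The preceding paragraph of the same section says how the condition is to be met: the work starts "After describing missing data and investigating the mechanism of missing data profiles". It then adds that "imputation will be performed using a multiple imputation method by sensitivity analysis after checking normality", in connection with the comparison of the two summary scores at 1 and 2 years. No departure from MAR is stated for that imputation, and no MNAR analysis of the SF-36 scores is planned unconditionally.

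Under Interventional study, the longitudinal comparison is secondary objective (3): "longitudinally: all HRQoL dimensions of the MOS SF-36 and the CarGOQoL questionnaire". The main objective is the comparison of the two summary scores at 1 year.

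**The concern.** MAR and MNAR differ only in how the unseen scores are distributed once everything observed is taken into account. For any MNAR distribution there is a MAR distribution that gives exactly the same observed data. An investigation of the collected data can therefore show that missingness depends on observed history, and so reject missing completely at random. It cannot go further. A conclusion that there is no MNAR profile carries no evidence for the assumption on which the mixed model rests, and a conclusion that there is one rests on judgement.

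MNAR loss is plausible here. Questionnaires are self-administered by post or online (Administration of questionnaires), and the outcome is the wellbeing of people who may be overburdened. Loss could also differ by arm. The intervention arm has social-worker visits scheduled every 6 months, while controls receive only the booklet unless they seek services themselves (Randomization procedure). The document does not say that loss will differ.

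At stake is whether the longitudinal arm and arm-by-time effects come with any indication of how far they depend on an assumption that cannot be checked.

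**Working it through.** **1. The plan's own loss figure.** Sample size calculation: 4 × 1684 + 488 = 7224 caregivers. Allowing for 5% loss, 7224 / 0.95 = 7604.2, which agrees with the stated 7604 (380 extra). Five per cent is the only loss figure in the document; any larger figure below is an assumption.

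**2. Can the trigger discriminate?** Take two simulated worlds with the same seed, 842 caregivers per arm, SD 25 and 300 runs. Missingness depends on arm and baseline score. In the first world the unseen scores follow their MAR prediction. In the second, the unseen scores of one arm are lowered by 10 points. Only unseen values change, so the observed data are identical in every run.

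| Overall share missing | Observed-data arm effect, both worlds | Full-data arm effect, MAR | Full-data arm effect, MNAR |
|---|---|---|---|
| about 6% | −0.07 | −0.08 | −0.80 |
| about 24% | −0.05 | −0.08 | −2.70 |

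Any diagnostic computed from the observed data gives the same answer in both worlds, although the true effects differ. The example is a baseline-adjusted comparison at one later time point, not the protocol's full repeated-measures model. It illustrates the identification problem and does not predict this trial's result.

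**3. Size of the error.** Let m be the share missing in an arm and s the mean distance of the unseen scores from their MAR prediction (negative means worse). At a given time point:

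true arm difference − MAR estimate = m_I × s_I − m_C × s_C

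With equal loss and a shift in the control arm only (s_I = 0):

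| Loss in each arm | s_C = −5 | s_C = −10 | Share of the 5-point MCID |
|---|---|---|---|
| 5% (protocol) | 0.05 × 5 = 0.25 | 0.05 × 10 = 0.5 | 5% to 10% |
| 20% (assumed) | 0.20 × 5 = 1.0 | 0.20 × 10 = 2.0 | 20% to 40% |

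A shift in the intervention arm instead reverses the sign, so the error can create an apparent effect or hide a real one. With the same loss and the same shift in both arms it vanishes: 0.05 × (−10) − 0.05 × (−10) = 0. At the other extreme, if all of a 5% overall loss fell in one arm, that arm would have 10% missing, and a 10-point shift would give 0.10 × 10 = 1.0 point.

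The identity fits the table in step 2. At about 24% missing the two worlds differ by 2.70 − 0.08 = 2.62 points, or 2.62 / 10 = 26% missing in the shifted arm, which the example gives a somewhat higher loss than the other.

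**4. Does the analysis set matter?** The Analysis section defines a modified intention-to-treat set of caregivers "with MOS SF-36 scores available at baseline and 1 year", and then says the interventional study is analysed by intention to treat. Whichever set is used for the longitudinal model, questionnaires missed after 1 year remain missing, so the point stands in both cases.

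**The case against.** The article prescribes no test, threshold or list of inputs for judging the mechanism. The research assistants telephone caregivers whose questionnaires are not back after 4 weeks, so reasons for non-return could inform a judgement that MNAR is plausible, and that is a legitimate ground for using a pattern mixture model. How the judgement is made, and which identifying restrictions are used, commonly belongs in the statistical analysis plan, which the article says will be written before database lock. The protocol also names multiple imputation as a sensitivity analysis.

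Part of this stands. The missing detail is not a fault, and reasons for non-return are useful information. But they can only make MNAR plausible; they neither establish it nor rule it out. No trigger written later can repair a rule that makes the two models alternatives, and that rule is fixed in the protocol. Multiple imputation does not close the gap, because no departure from MAR is stated for it and it is described for the comparisons at 1 and 2 years.

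A reader might infer that the MNAR analysis will never be run. The documents do not support that: whether it runs depends on how the mechanism is judged, and a criterion that reacts to any dependence on observed history could select pattern mixture almost always. The complaint is that the choice is uninformative in both directions.

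**Conclusion.** The point holds as a badly fixed rule for a secondary analysis. The switch asks the data a question they cannot answer, and only one of the two models need then be reported.

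Three stronger readings should be resisted. First, the primary 1-year comparison is not affected, because no switch is stated for it. Second, the longitudinal effect is not shown to be biased: with the same loss and shift in both arms there is no bias, and at the planned 5% loss it is 0.25 to 0.5 points for a 5 to 10 point shift in one arm, with equal loss. Third, no false-positive rate can be attached to the rule from the documents, because that would need the correlation structure of the repeated-measures model and the actual loss, and neither is given.

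The error becomes material, 1 to 2 points against the 5-point MCID, only if loss over the repeated assessments reaches something like the assumed 20% and the unseen scores shift in one arm. The shifts, the equal split of loss and every loss above 5% are assumptions. The 5-point MCID was set for the summary scores; using it as a yardstick for the individual dimensions or for CarGOQoL is a further assumption.

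**What to change.** Remove the data-driven switch. Fit the mixed model under MAR as the main longitudinal analysis. Beside it, whatever the description of missing data shows, always report a prespecified pattern mixture (delta-adjusted) sensitivity analysis in which unseen scores are shifted over a range set separately for each arm, for example 0, −5 and −10 points, scaled to the MCID. State the shift at which the conclusion on the arm effect changes. A range is needed because a pattern mixture model rests on untestable restrictions of its own. Keep the description of missingness by arm, with any recorded reasons for non-return, as a guide to which shifts are plausible and not as a selector of the model.

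The cost is a sentence in the Analysis section, the corresponding text in the statistical analysis plan before database lock, and some programming. No extra caregivers or data are needed. The downside is that the conclusion may have to be reported as sensitive to missing data.
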